# 14. Assessment schedule

Outcome assessments will be conducted by trained assessors blinded to treatment allocation. Assessments will take place at baseline, week 4, week 12, and week 24. Primary and secondary outcomes will be collected at each assessment time point where applicable.

| Outcome | Baseline | Week 4 | Week 12 | Week 24 |
| --- | --- | --- | --- | --- |
| Pain intensity | Yes | Yes | Yes | Yes |
| Oswestry Disability Index | Yes | Yes | Yes | Yes |
| Secondary outcomes | Yes | Yes | Yes | Yes |

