# 16. Sample size calculation

The sample size was calculated based on detecting a clinically meaningful between-group difference of 2 points on the 0-10 numerical rating scale for pain intensity. The assumptions were: standard deviation of 3, power of 80%, and two-sided alpha of 0.05.

This required 86 participants per group. Allowing for 20% attrition, the final target sample size is 208 participants, with 104 participants per group.

The study is powered based on the primary outcome of pain intensity. Although repeated measurements will be collected over time, the planned linear mixed-effects modelling approach will account for within-subject correlation and is expected to increase statistical efficiency.

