# 17. Statistical analysis

All analyses will follow the intention-to-treat principle.

Primary outcomes will be analysed using linear mixed-effects models. The models will include group, time, and group-by-time interaction as fixed effects, and participant as a random effect.

Continuous secondary outcomes will be analysed using similar mixed-effects models where appropriate. Categorical outcomes will be analysed using logistic regression or chi-square tests. Post-hoc comparisons will be adjusted using Bonferroni correction where appropriate.

Missing data will be handled using Multiple Imputation by Chained Equations under the assumption that data are missing at random. The imputation model will include baseline outcomes, treatment allocation, and relevant demographic variables. At least 20 imputations will be generated.

To assess potential attrition bias, baseline characteristics of participants who complete the study and those who do not will be compared.

A per-protocol sensitivity analysis will include participants who complete at least 80% of treatment sessions. All statistical analyses will be conducted using SPSS version 29.0 or later. Statistical significance will be set at p < 0.05.

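### Post-hoc comparisons: naming Holm's step-down instead of Bonferroni would be a cheap gain in power at the same nominal familywise error; the present choice is valid and is not an error

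*Protocol*

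**What the plan says.** Section 17 of the protocol fits linear mixed-effects models with group, time and their interaction. On multiplicity it then has one sentence: "Post-hoc comparisons will be adjusted using Bonferroni correction where appropriate". The overall threshold is given as "Statistical significance will be set at p < 0.05".

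The protocol does not say which comparisons count as post-hoc, how many there are, or how they are grouped into families. It names no other correction. Section 14 sets the visits: "Assessments will take place at baseline, week 4, week 12, and week 24".

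Section 16 gives the only effect size, a "clinically meaningful between-group difference of 2 points on the 0-10 numerical rating scale for pain intensity", with "standard deviation of 3, power of 80%, and two-sided alpha of 0.05". It claims no power for any post-hoc comparison.

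**The concern.** Single-step Bonferroni holds every comparison in a family of m to 0.05/m, even after others in the family have been declared significant. Holm's procedure relaxes the threshold as hypotheses are rejected, and needs no assumption about the correlation between tests to keep familywise error at 5%. When the aim is only to decide which comparisons are significant, Holm can do no worse.

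At stake is power for the weaker contrasts in a family. Treatment lasts four weeks and follow-up runs to week 24, so an effect that shrinks after treatment ends is plausible, although the protocol does not predict one. In that case the later contrasts, which bear on durability, are the ones most likely to miss the Bonferroni threshold and pass Holm's.

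**Working it through.** **The plan's own figure.** There is none for post-hoc power, so nothing can be reproduced directly. The nearest is section 16: "This required 86 participants per group". The usual formula with its inputs gives n = 2 × 3² × (1.960 + 0.842)² / 2² = 35.3, so 36 per group, not 86. That is a separate matter. The check below uses the stated enrolment.

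**Inputs from the protocol.** SD 3, two-sided alpha 0.05, a 2-point difference, 104 per group, 20% attrition, and post-baseline visits at weeks 4, 12 and 24.

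**Assumptions not in the protocol.**
- The family is the three active-versus-sham contrasts for one outcome, so m = 3.
- 104 × 0.8 = 83.2, so 83 evaluable per arm.
- The visit-wise test statistics are normal, with correlation 0.5 to 0.7.
- The fading effect is 2.0, 1.28 and 1.0 points.

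**The rules.** Bonferroni rejects where p < 0.05/3 = 0.0167. Holm orders the p-values and compares the smallest with 0.05/3 = 0.0167, the next with 0.05/2 = 0.025 and the largest with 0.05, stopping at the first failure. As an illustration, take p-values of 0.001, 0.020 and 0.040. Bonferroni rejects one. Holm rejects all three. Holm's first step is the Bonferroni test of the smallest p-value, so the two always agree on whether anything is rejected.

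**Bonferroni power in closed form.** SE = 3 × √(2/83) = 0.466. The critical value at 0.0167 two-sided is 2.394. Power is approximately Φ(difference/SE − 2.394):
- 2.0 points: Φ(4.295 − 2.394) = Φ(1.901) = 97.1%
- 1.28 points: Φ(2.749 − 2.394) = Φ(0.355) = 63.9%
- 1.0 point: Φ(2.147 − 2.394) = Φ(−0.247) = 40.3%

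**Holm power by simulation** (400,000 draws per scenario, 83 per arm, ranges over correlation 0.5 to 0.7):

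| True difference at weeks 4 / 12 / 24 | Quantity | Bonferroni | Holm |
| --- | --- | --- | --- |
| 2 / 2 / 2 | power at each visit | 97% | 99% |
| 2 / 2 / 2 | all three visits | 93-94% | 97-98% |
| 2.0 / 1.28 / 1.0 | power at week 12 | 64% | 71-72% |
| 2.0 / 1.28 / 1.0 | power at week 24 | 40% | 54-55% |
| 1.28 / 1.28 / 1.28 | power at each visit | 64% | 71-72% |
| 1.28 / 1.28 / 1.28 | all three visits | 39-46% | 57-61% |
| 0 / 0 / 0 | familywise error | 4.0-4.4% | 4.0-4.4% |
| 2 / 0 / 0 | familywise error | about 3% | 4.0-4.5% |

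Before rounding, the per-visit gain for a constant 2 points is under 2 points of power (97.1% to between 98.5% and 98.8%). No draw contained a Bonferroni rejection that Holm missed, and the chance of at least one rejection was the same for both in every scenario.

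**Sensitivity to sample size.** With all 104 per arm and the fading pattern, week 12 goes from 75% to 81-82% and week 24 from 50% to 65%. With 86 per arm and a pattern of 2, 1.5 and 1 points, week 24 goes from 42% to 57-58%.

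**The case against.** The strongest reply is that nothing here is wrong. Bonferroni is a valid, conservative correction, the sentence contradicts nothing else in the protocol, and choosing between two valid methods is a matter of preference. That stands, and it is why this is offered only as an improvement.

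Three stronger readings are tempting, and the documents support none of them:

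- *The plan is locked into Bonferroni.* The sentence leaves its use to judgement and defines no family. Bonferroni is the only method named, which is a weaker statement.
- *The plan loses power at weeks 12 and 24.* The protocol never says that the post-hoc comparisons are between-group contrasts at those visits; they could be within-group changes over time. The dominance of Holm holds for any family of two or more, but the sizes above belong to the assumed family of three. At the protocol's own 2-point difference the loss is negligible. The larger losses need differences of 1.28 and 1.0 points, which the protocol does not give.
- *The power is given up for nothing.* Bonferroni has simple simultaneous confidence intervals that match its tests, and Holm does not. When only some contrasts are null, Bonferroni is also stricter: with a true difference of 2 points at week 4 and none later, familywise error is about 3%, against 4.0-4.5% for Holm.

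Against the last point, both methods stay within 5%, and the protocol plans no simultaneous intervals, so nothing it promises would be lost.

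**Conclusion.** The point holds as a cheap improvement. For decisions at a nominal familywise 5%, Holm rejects everything Bonferroni rejects and sometimes more, whatever the correlation and whatever the family. That part needs no assumption about this trial.

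The size of the gain does. With a family of three visit contrasts, 83 per arm, SD 3 and correlation 0.5 to 0.7, it is under 2 points of power per visit for a constant 2-point difference. For a fading effect of 2.0, 1.28 and 1.0 points it is about 8 points at week 12 and about 14 at week 24. The chance of finding at least one difference does not change. The protocol neither states nor implies the fading pattern, so the larger figures show what could be gained and do not forecast a loss.

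**What to change.** In section 17, replace *Bonferroni correction* with *Holm's step-down procedure (Holm-Bonferroni)* and leave the rest of the sentence as it is. The sponsor should choose the family; this point does not depend on that choice.

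The edit is a few words. Section 5 reports no enrolment at protocol submission, so if that is still so it can be made before there are any data. Holm-adjusted p-values follow by hand from the unadjusted ones: for three tests, multiply the smallest by 3, the next by 2 and the largest by 1, carry the running maximum forward, and cap at 1.

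There are two costs. Unadjusted 95% intervals reported alongside may not always agree with the adjusted tests, so the report should say that they are unadjusted. Holm also uses more of the 5% allowance when only some contrasts are null. If the sponsor wants simultaneous intervals that match the tests, keeping Bonferroni is a sound choice.

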# 18. Safety monitoring and adverse event reporting

CSWD is a non-invasive intervention and is expected to involve minimal risk. Potential adverse effects include mild warmth, temporary discomfort, or transient symptom aggravation.

An adverse event will be defined as any undesirable experience occurring during the trial, whether or not considered related to the intervention. A serious adverse event will include any event resulting in death, life-threatening illness, hospitalisation, significant disability, or any medically important event.

All adverse events will be recorded at each treatment visit and follow-up assessment. Serious adverse events will be reported to the Ethical Review Committee within 24 hours.

A trial steering committee will supervise protocol adherence, safety monitoring, and data integrity. Given the non-invasive nature of CSWD, a formal Data Safety Monitoring Board is not planned.

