# 3. Study design

This study is a multicentre, two-arm, parallel-group, randomised, single-blind, sham-controlled clinical trial.

Participants will be randomly allocated in a 1:1 ratio to one of two groups: active CSWD plus standard physiotherapy, or sham CSWD plus standard physiotherapy.

Participants and outcome assessors will be blinded to treatment allocation. Treating physiotherapists cannot be blinded because active CSWD produces perceptible warmth.

Outcome assessments will be conducted at baseline, week 4, week 12, and week 24. The total follow-up period will be 24 weeks.

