# 9. Randomisation and allocation concealment

Randomisation will be conducted using a computer-generated random allocation sequence. Permuted block randomisation with block sizes of 4 and 6 will be used and stratified by centre.

Allocation concealment will be maintained using sequentially numbered, opaque, sealed envelopes prepared by an independent researcher who is not involved in participant recruitment, treatment delivery, or outcome assessment.

After baseline assessment and informed consent, the treating physiotherapist will open the next sequential envelope to determine group allocation.

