# 10. Blinding

Participants and outcome assessors will be blinded to treatment allocation. Treating physiotherapists cannot be blinded because active CSWD produces a perceptible heating sensation.

To maintain participant blinding, both groups will receive identical positioning and device placement. Device appearance will be identical in both groups where possible. Participants in both groups will be informed that the perception of warmth varies between individuals.

At week 4, participants will be asked to guess their group allocation to assess blinding success.

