# 11. Interventions

All participants will receive a standardised physiotherapy programme three times per week for four weeks. The only difference between groups will be whether CSWD is active or sham.

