# 12. Intervention standardisation and adherence

All physiotherapists involved in treatment delivery will receive structured training before study initiation using a standardised treatment manual. The training will include CSWD safety procedures, electrode placement, sham procedures, exercise delivery, participant education, and adverse event documentation.

Treatment fidelity will be monitored using standardised treatment checklists, periodic site supervision, and trial steering committee oversight.

Attendance will be recorded at each treatment session. Participants who complete at least 80% of scheduled treatment sessions will be considered adherent for per-protocol analysis.

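### Adverse events in weeks 1-4 are probably recorded by unblinded physiotherapists, so any description of harms by arm is open to observer bias (minor; cheap to fix)

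*Protocol*

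**What the plan says.** Section 18 sets the timing: "All adverse events will be recorded at each treatment visit and follow-up assessment". It also sets the scope: "An adverse event will be defined as any undesirable experience occurring during the trial, whether or not considered related to the intervention". The effects it expects are warmth, discomfort and a passing worsening of symptoms. The section does not say who records events at a treatment visit, or what the participant is asked.

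The staff at those visits are described elsewhere in the protocol:

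- Section 11 fixes the number of visits: "All participants will receive a standardised physiotherapy programme three times per week for four weeks".
- Section 9 says that "the treating physiotherapist will open the next sequential envelope to determine group allocation".
- Section 3 says "Treating physiotherapists cannot be blinded because active CSWD produces perceptible warmth", and section 10 repeats this in nearly the same words.
- Section 12 describes how the physiotherapists who deliver treatment are prepared: "The training will include CSWD safety procedures, electrode placement, sham procedures, exercise delivery, participant education, and adverse event documentation".

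Blinded staff appear in section 14: "Outcome assessments will be conducted by trained assessors blinded to treatment allocation". These assessments fall at baseline and weeks 4, 12 and 24. Adverse events are not in the outcome lists of section 13 or in the section 14 table.

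**The concern.** The active device works only in weeks 1-4, and in that period adverse events are taken at visits run by someone who knows the arm. What counts as an event is a matter of judgement. Under section 11.2, active treatment is adjusted until it gives comfortable warmth, while section 18 lists mild warmth as a possible adverse effect. A physiotherapist who knows that the device is on may enter a complaint as an event or treat it as the intended effect. One who knows that the device is at 0 W may discount the same complaint. Under-recording could therefore occur in either arm.

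At stake is the credibility of any table of harms by arm. The trial has a sham control and blinded participants, so it could describe harms even-handedly. Unequal recording arises when the data are collected, and no later analysis can repair it.

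**Working it through.** **Step 1. Who is present, and what they know.** There is no figure in the plan to reproduce, so the sections are set side by side.

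| Question | Treatment visits | Follow-up assessments |
|---|---|---|
| How many | 3 per week x 4 weeks = 12 (section 11) | 3: weeks 4, 12 and 24 (section 14) |
| Staff described | Treating physiotherapists (sections 9, 12) | Outcome assessors (section 14) |
| Know the allocation | Yes (sections 3, 9, 10) | No (sections 3, 10, 14) |
| Adverse events recorded | Yes (section 18) | Yes (section 18) |
| Recorder named | No; physiotherapists are trained for it (section 12) | No; assessors are named only for outcomes (section 14) |

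That the physiotherapist records events at treatment visits is a strong inference from sections 9 and 12, not a statement in the text.

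**Step 2. Does the text secure equal recording between arms?** Section 4 requires identical data-collection and safety-monitoring procedures at all centres. That addresses differences between centres, not between arms within a centre. The checklists and site supervision in section 12 serve treatment fidelity. No section gives a common question, or a blinded source, for the treatment visits.

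**Step 3. What unequal recording would do.** Suppose the true proportion of participants with an event is p in both arms, and that such a participant is recorded with probability a in one arm and b in the other. The apparent risk ratio is (p x a) / (p x b) = a / b, so p cancels. The values of a and b are assumptions; the protocol gives nothing on them.

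| Recorded (a against b) | Apparent risk ratio | If the arms are reversed |
|---|---|---|
| 90% against 90% | 1.00 | 1.00 |
| 90% against 70% | 1.29 | 0.78 |
| 90% against 60% | 1.50 | 0.67 |
| 90% against 50% | 1.80 | 0.56 |

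**Step 4. Would it be visible in this trial?** Take p = 10%, 104 per arm (section 16), and recording of 90% against 60%. The expected counts are 0.09 x 104 = 9.4 and 0.06 x 104 = 6.2, or about 9 against 6. For 9 against 6:

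- pooled proportion = 15/208 = 0.072
- standard error = sqrt(2 x 0.072 x 0.928 / 104) = 0.036
- z = (0.0865 - 0.0577) / 0.036 = 0.80, so p is about 0.42.

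A result like this would pass unnoticed in a significance test, yet would still colour a descriptive table. For true risks of 10% to 30%, a two-sided 5% test with 104 per arm would be falsely significant in the direction of the bias with probability 8-17% (90% against 70%) or 20-57% (90% against 50%). The nominal level in one direction is 2.5%. The protocol plans no such test, so these figures only indicate scale.

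**The case against.** **No harm comparison is planned.** Adverse events are not among the objectives (section 2) or outcomes (section 13), and section 17 gives no analysis of them. Section 18 treats them as safety monitoring. This stands. A reader might infer that the harm contrast carries much of the fourth secondary objective, on clinically useful additional benefit, but that objective speaks of benefit and does not mention harm. What remains is any by-arm description of harms, including a purely descriptive one.

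**The recorder is inferred.** This also stands. A reader might infer that the harm comparison is biased. The documents support only that it is open to bias.

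**There are safeguards.** Participants are blinded by design. All events count whether or not they are thought related, which removes the causality judgement from the decision to record. There is a treatment manual, training and steering committee oversight. Follow-up visits also record events, and week 4 coincides with the end of treatment. A reader might infer that nearly all the relevant harm data come from an unblinded source. That is not established, because blinded assessors may collect adverse events at week 4. But the protocol does not say that they do, or that they ask about the whole treatment period.

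**Question wording and order belong in the forms or the manual.** This is largely fair for layout, and it is one reason to rate the point low. Which source is blinded is a matter of design, however, and one sentence in the protocol can settle it.

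**A fuller remedy could do harm.** A symptom checklist that names heat, completed at up to 12 sessions, could keep reminding sham participants that they feel none. That could weaken the blinding on which the self-reported primary outcomes rest. This objection is sound, and the fix below avoids such a checklist.

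**Conclusion.** The point holds as a minor one. Adverse events in weeks 1-4 are taken at up to 12 visits per participant run by unblinded physiotherapists, who are the likely recorders. With an open definition and subjective expected effects, any active-versus-sham description of harms is open to observer bias. Its size and direction are unknown: the risk ratios of 0.56 to 1.80 follow from assumed recording rates of 50% to 90% and predict nothing about this trial.

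Two limits apply. Hard serious events leave little room for judgement and are little affected. The pain and disability analyses do not use these records, so a reader should not infer that the efficacy result is in doubt.

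**What to change.** Amend sections 12 and 18 as follows.

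1. At each session, in both arms, ask the same scripted open question, which must not name warmth or heat (for example, whether anything unwanted has happened since the last session). Write down the participant's answer verbatim. Events that the physiotherapist observes go on a separate line.
2. At weeks 4, 12 and 24, have the blinded assessor ask about adverse events only after all outcome questionnaires are complete, so that a remark about the device cannot reach the assessor first. At week 4 the question covers the whole treatment period.
3. Use the participant-reported and blinded-assessor records as the source for any harm table by arm. Keep the physiotherapists' records for safety reporting, which is unchanged.

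The cost is one extra line per session form, at most 12 x 208 = 2,496 lines under the double data entry of section 15, and somewhat more minor events recorded in both arms. No extra staff are needed. Section 5 reports that nobody had been enrolled when the protocol was submitted; if that is still so, the change can be in place before any data exist.

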# 19. Ethical considerations

Ethical approval has been obtained from the Ethical Review Committee of Uttara Adhunik Medical College.

Ethics reference number: UAMC/IRB/ERC/Recommend-01/2025. Approval date: 30 September 2025.

Written informed consent will be obtained from all participants before any study procedures are undertaken. Participation will be voluntary. Participants may withdraw at any time without penalty or effect on their usual care.

The trial is registered with the Clinical Trials Registry-India. Trial registration number: CTRI/2025/11/097194. Registration date: 11 November 2025.

# 20. Confidentiality

Participant confidentiality will be maintained throughout the study.

All personal information will be stored securely and separately from study data. Study data will be identified using coded participant numbers rather than names or other direct identifiers.

Only deidentified, aggregated findings will be reported in publications and presentations.

